## Abstract

**Introduction:**

In the UK, about a quarter of women give birth by caesarean section (CS) and are offered prophylactic broad-spectrum antibiotics to reduce the risk of maternal postpartum infection. In 2011, national guidance was changed from recommending antibiotics after the umbilical cord was cut to giving antibiotics prior to skin incision based on evidence that earlier administration reduces maternal infectious morbidity. Although antibiotics cross the placenta, there are no known short-term harms to the baby. This study aims to address the research gap on longer term impact of these antibiotics on child health.

**Methods and analysis:**

A controlled interrupted time series study will use anonymised mother-baby linked routine electronic health records for children born during 2006–2018 recorded in UK primary care (The Health Improvement Network, THIN and Clinical Practice Research Datalink, CPRD) and secondary care (Hospital Episode Statistics, HES) databases. The primary outcomes of interest are asthma and eczema, two common allergy-related diseases in childhood. In-utero exposure to antibiotics immediately prior to CS will be compared with no exposure when given after cord clamping. The risk of outcomes in children delivered by CS will also be compared with a control cohort delivered vaginally to account for time effects. We will use all available data from THIN, CPRD and HES with estimated power of 80% and 90% to detect relative increase in risk of asthma of 16% and 18%, respectively at the 5% significance level.

**Ethics and dissemination:**

Ethical approval has been obtained from the University of Birmingham Ethical Review Committee with scientific approvals obtained from the independent scientific advisory committees from the Medicines and Healthcare products Regulatory Agency for CPRD and the data provider, IQVIA for THIN. The results will be published in peer-reviewed journals, presented at national and international conferences and disseminated to stakeholders.

Strengths and limitations of this studyA large sample size including mother-child linked data from two nationally representative primary healthcare databases and a secondary healthcare database.Investigation of a broad range of relevant child outcomes including severity.Investigation of maternal outcomes using real world evidence to confirm findings reported in randomised controlled trials.Use of a comparison group of vaginally delivered children to effectively control for changes in diagnosis, recording and exposures over time.Timing of prophylactic antibiotic administration is not recorded in routine healthcare data; therefore, analysis is based on the estimated proportion of hospitals with the preincision antibiotic policy in each year during the study period.

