We have a proposed linkage strategy which has already been validated by another recent study using matching algorithms based on HES data using organisation codes, admission dates, birth dates, general practice codes, sex, gestation and maternal age plus a number of other variables common to birth and maternity records. The database remains nationally representative for the main birth characteristics (such as gestational age, birth weight, sex and maternal age).^27^ The final output of this process will be a linked HES data set in which details of birth events and subsequent admissions of the children associated with these events can be elucidated.

HES alone, however, cannot be used to identify timing of prophylactic antibiotic administration and prophylactic antibiotics given. We will obtain the time point after which preincision antibiotic policy was introduced in each hospital from a national survey of maternity care providers in the UK. All maternity units undertaking CSs were included in the survey with a target response rate of 85%.

The exposure and outcome measures in the healthcare databases will be defined using the Read clinical code classification system used in primary care, and International Statistical Classification of Diseases and Related Health Problems 10th Revision (ICD-10) used for clinical diagnoses, the Office of Population Censuses and Surveys Classification of Surgical Operations and Procedures 4th revision (OPCS) for procedures and Healthcare Resource Groups (HRG) codes used in HES.

Recording of some variables in healthcare data, such as breastfeeding, is incomplete; we will therefore also investigate the trends in these variables by the mode of delivery using additional data sources such as the National Maternity Surveys.^28^

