### Methods

We will compare rates of diagnosis of asthma and other outcomes of interest over time in children born by CS, comparing outcomes according to whether each mother received preincisional antibiotics.

In the primary analysis, we will estimate a probability that each mother received preincisional antibiotics according to year of birth, based on national policy uptake rates in the year of delivery for primary care data. For secondary care data, we will use the response from each hospital indicating the year of local policy implementation.

The major threat to validity in this observational comparison is not from case-mix confounders (indications for and incidence of CS have changed little over the study period); rather they relate to temporal changes in diagnosis and in the recording of outcomes and other exposures which impact on the number of cases identified in routine data. Patterns of diagnosis of childhood asthma, for example, have changed over time, in part driven by the revisions in the national asthma management guideline and the potentially conflicting compliance and prevalence issues faced in meeting specific indicators of the Quality and Outcomes Framework (QOF) introduced in 2004.^29 30^

An analysis reliant on adjustment for confounding factors is unlikely to succeed in controlling for these changes as it is unclear (1) what all the drivers of all these changes have been, (2) whether any covariates exist which accurately describe these changes without substantial missing data and (3) challenges in specification of a functional form for the relationship between these covariates and outcome.

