Outcome events were randomly simulated according to the year-age event rates using a binomial random number generator, with increased rates in all those delivered by CS, and increased further in those who received antibiotics before skin incision. A risk ratio of 1.2 was used for increased risk of asthma with CS^32^ and then further increases with risk ratios from RR=1.10 to RR=1.20 (increasing in steps of 0.02) for the increase with antibiotics before skin incision rather than after cord-clamping.

Simulations were repeated 1000 times, and statistical power estimated by noting the proportion of simulations for which the lower limit of the 95% CI for the variable indicating whether antibiotics were given before skin incision was greater than a risk ratio of 1. We also recorded the estimates of the relative risk to assess attenuation bias created by misclassification.

The model which we fitted to analyse the simulation data included a trend term for the probability of receiving preincisional antibiotics with values 2006–2009=0, 2010=0.2, 2011=0.4, 2012=0.6, 2013=0.8, 2014–2018=1 with a zero value for those delivery vaginally (in the final analysis, we will use probabilities for each year obtained from the survey).

For the primary care data, we have 80% power of detecting a 16% relative increase in risk of asthma and over 90% power of detecting an 18% relative increase in risk, and being able to estimate them with a maximum of 15% underestimation from misclassification. For the HES admission data, we have over 80% power to detect a 10% relative increase in risk of asthma and 90% power to detect a 12% relative increase in risk with similar rates of underestimation due to misclassification.

The study will also be adequately powered to detect differences in the other primary outcome of interest (eczema) as incidence of clinician-diagnosed eczema is higher than asthma incidence in children in the UK.^33–35^

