#### Sensitivity analyses

Sensitivity to population changes:

Analysis assessing the impact of the timing of the prophylactic antibiotic policy change, including comparison of analysis restricted to the years 2006–2010 (before the change in the NICE guideline) compared with years where over 50% of hospitals had introduced the policy.Analysis of the primary outcomes in the full HES dataset (including data for the hospitals that do not respond to the survey and therefore preclude us linking information about prophylactic antibiotic policy at hospital level) using the estimated probability of introduction of preincisional antibiotics according to calendar year, to investigate the consistency of findings.Analysis investigating the impact of the data recording quality (restricted to HES-linked records in THIN-CPRD database as the most accurate source of records for the mode of delivery).Exploratory sensitivity analysis employing the discordant sibling approach (restricting the analysis to women who gave birth by CS more than once during the study period including before and after the change in the prophylactic antibiotic policy compared with women who gave birth by VD more than once during the study period) to control further for family-related genetic and environmental factors.

Sensitivity to model changes:

Analysis exploring whether the results are robust to the inclusion of a random effect for hospital.

Subgroup analyses:

Exploratory subgroup analysis in HES mother-child linked database by prophylactic antibiotic type administered according to the individual hospital policies to investigate the potential impact of different antibiotics (cefuroxime alone, co-amoxiclav alone, cefuroxime+metronidazole) on child outcomes.Exploratory subgroup analysis by the type of CS (it is hypothesised that children delivered by elective CS have a higher likelihood of asthma and related outcomes and are more likely to be exposed to in-utero antibiotics for longer than children born to women having an emergency CS).

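### The yearly exposure probability is described as a share of hospitals, but the analysis needs the share of caesarean births in those hospitals; they agree only if unit size and adoption date are unrelated

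*Protocol article*

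**What the plan says.** In the Methods section the exposure for primary care is set for the individual mother: "we will estimate a probability that each mother received preincisional antibiotics according to year of birth, based on national policy uptake rates". The sample size section adds that "in the final analysis, we will use probabilities for each year obtained from the survey", and Data sources describes that survey as one of maternity units: "All maternity units undertaking CSs were included in the survey with a target response rate of 85" per cent. The place that says what the yearly figure counts is the strengths and limitations list after the abstract: "analysis is based on the estimated proportion of hospitals with the preincision antibiotic policy in each year during the study period". The first sensitivity analysis also counts by hospitals when it picks the years in which more than half had adopted. Nowhere does the article weight units by their CS births.

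For the main HES analysis the rule differs: "we will use the response from each hospital indicating the year of local policy implementation". The HES sensitivity analysis that adds non-responding hospitals goes back to a yearly figure, "using the estimated probability of introduction of preincisional antibiotics according to calendar year, to investigate the consistency of findings".

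**The concern.** A share of hospitals gives a small unit the same weight as a large one. A mother's chance of delivering under the policy depends on where CS births take place. If large units tended to adopt earlier or later than small ones, the hospital share misstates that chance during the rollout, and in later years too if some units never adopt.

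This variable carries the key coefficient of the main primary-care analysis. The Analysis section says that coefficient adjusts for misclassification, which holds only if the probabilities are right for mothers. The sample size section allows for underestimation of up to 15%; an error in the denominator can go either way. The Aim section intends to set the magnitude of any risk against maternal benefit, so the size of the effect matters as well as its presence. The full-HES sensitivity analysis is a consistency check, and a denominator error could create or hide a small discrepancy there.

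**Working it through.** **The plan's own figures.** The article gives no figure for this error. Its 80% power at RR 1.16 could not be reproduced, because the age-by-year rates and exact model form are not given: expected-count Poisson fits scaled to Table 2 give 95-99.9% without a mode-by-year trend and 21-40% with a linear one or in CS-only models. The standard error (SE) implied by the stated power is log(1.16)/(1.96 + 0.84) = 0.148/2.80 = 0.053, used below as a yardstick.

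**Inputs.** From the sample size section: planning uptake "2006–2009=0, 2010=0.2, 2011=0.4, 2012=0.6, 2013=0.8, 2014–2018=1", follow-up to age 5 or the end of 2018, RR 1.16. Assumed, because the article gives no data: the relation between unit size and adoption date, equal births per year, births at mid-year, and the event-rate pattern.

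**Step 1: error in the yearly probability.** Let the larger half of units hold a share w of CS births and adopt L years before the rest, with uptake rising 0.2 a year. The birth share minus the hospital share is d = (w - 0.5) x 0.2L.
- w = 0.65, L = 1: 0.15 x 0.2 = 0.03.
- w = 0.75, L = 2: 0.25 x 0.4 = 0.10.
- If the larger units adopt later, the sign reverses. If size and date are unrelated, d = 0.

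**Step 2: effect on the estimate, simple case.** With a flat event rate and no mode-by-year trend, the coefficient is multiplied by about 1 + S(pd)/S(pp). These are sums over birth years, weighted by follow-up years and centred on the mean of p.
- Follow-up years per birth: 5 for 2006-2013, then 4.5, 3.5, 2.5, 1.5, 0.5; total 52.5.
- Weighted sum of p: 5 x 2.0 + 12.5 = 22.5, mean 0.4286. Weighted sum of p squared: 5 x 1.2 + 12.5 = 18.5.
- S(pp) = 18.5 - 22.5²/52.5 = 8.857.
- With constant d in 2010-2013, S(pd) = 5d x (2.0 - 4 x 0.4286) = 1.429d.
- Multiplier: 1 + 0.161d, so 1.005 at d = 0.03 and 1.016 at d = 0.10.

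The effect is small because errors in years below and above the mean of p partly cancel. Poisson fits under the same flat-rate assumptions give about 0.2-1.3% of the excess risk without a year-by-mode term and 0.6-3.2% with a linear one. The latter depends on how the lag is spread: a constant error of 0.10 in all four rollout years gives about 4.5% with the linear term. The Analysis section names an interaction of year with mode but not its form, so both cases are relevant. The sign differs between them: early adoption by large units inflates the estimate slightly without the trend and deflates it with one.

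**Step 3: stronger assumptions.** If log unit size has SD s and correlation r with adoption time, the birth share is Φ(z(p) - s·r). With s = 0.5 and r = -0.6, hospital shares 0.20/0.40/0.60/0.80 become 0.29/0.52/0.71/0.87; with r = +0.6 they become 0.13/0.29/0.48/0.71. The fits below assume an event rate that rises with age and falls 6% a calendar year. Flat rates mostly give smaller figures.

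| Setting | Bias in log RR at RR 1.16 |
|---|---|
| s 0.3-0.7, absolute r 0.3-0.6, no mode-by-year trend | -6% to +4% |
| Same, linear mode-by-year trend | -13% to +5% |
| Uptake levels off at 0.85, s 0.5-0.7, absolute r 0.6, no trend | -18% to +13% |
| RR = 1, any setting | none |

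The plateau matters because the error then persists after the rollout: with s = 0.5 and r = +0.6, z(0.85) - 0.3 = 0.736, so the birth share is 0.769 and 0.769/0.85 = 0.90.

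**Against sampling error.** 3% of an excess of 0.16 is 0.005, so RR 1.16 is estimated at about 1.155 to 1.165, under a tenth of an SE. The extreme of 18% is 0.18 x 0.148 = 0.027, about half an SE.

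**The case against.** The best defence is that the wording about hospitals sits in a summary bullet. Taken literally, that bullet does not even describe the main HES analysis. The operative text speaks of national uptake rates, survey probabilities and a probability of preincision antibiotics, none of which rules out weighting. How survey replies become a yearly figure is detail an article may leave to the full plan. The bullet also discloses the approximation, and the main HES analysis with hospital-level policy years stands beside the primary-care one.

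Much of this stands. A reader might infer that the protocol has definitely fixed an unweighted count, or contradicts itself. The documents do not support that: the full plan may already weight. A reader might also infer that large units did adopt earlier or later; nothing in the article links size to adoption. Nor does the error produce a false signal, since there is no bias at RR 1. And it does not usually take up much of the 15% the protocol allows for: in simple settings it is a small part of that.

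What remains is that the wording which names a denominator names hospitals, the quantity needed is for mothers, and following the text as written gives a less accurate exposure whenever size and date are related. The repair is a specific, better definition, not just a request for more detail.

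**Conclusion.** The point holds as a definition to correct, with a conditional and usually small effect. It rests on two things: that the yearly figure is an unweighted hospital share, as the article describes it, and that adoption date is related to unit size, which is unknown. If both hold, the size of a true effect is biased in either direction, by roughly 0-3% of the excess risk at RR 1.16 in simple settings. A mode-by-year trend adds to this, and about 10-18% is reached only when strong size-by-date correlations combine with such a trend or with a plateau in uptake below 100%. It affects the main primary-care analysis and the full-HES sensitivity analysis, but neither the main HES analysis nor a test of the null. It should be changed because the change is easy and removes an untested assumption from the key variable, not because the conclusions are in danger.

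**What to change.** Define the yearly probability as the CS-birth-weighted proportion over responding hospitals: CS births in that year in hospitals with the policy in force, divided by all CS births in responding hospitals that year. Take CS counts by hospital and year from HES for England, and published or survey unit birth counts elsewhere in the UK. Use this figure in the main primary-care analysis and in the full-HES sensitivity analysis, reword the limitation to match, and report results with the unweighted hospital share as a sensitivity analysis. If the full plan already weights this way, only the wording needs changing.

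The cost is an extra data step, plus another source for unit totals outside England. Weighting does not repair survey non-response, and national weights remain a proxy for the hospitals used by mothers in the primary-care sample.

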## Introduction

Births by caesarean section (CS) account for over 20% of births globally and are increasing.^1^ Over one in four babies in the UK are born by CS.^2–5^ CS is a surgical procedure and women undergoing CS are at increased risk of developing infections after giving birth which can be prevented by prophylactic antibiotics. Before 2011, the national guidance advised administering intravenous prophylactic antibiotics for women undergoing CS after the baby’s cord had been clamped to prevent exposing the baby to antibiotics. In 2011, the guidance was changed to recommend giving antibiotics to women undergoing CS prior to skin incision. This was based on evidence that earlier administration reduces maternal infectious morbidity.^6^ The current Cochrane review summarises data from 10 randomised trials (5041 women) which showed a near halving of risk of all postpartum maternal infection (43%, 95% CI 28% to 55%), endometritis (46%, CI 21% to 64%) and wound infection (41%, CI 19% to 56%) compared with giving antibiotics after clamping the baby’s umbilical cord.^7^ Most postpartum maternal infections, however, are mild and respond well to treatment.^8^

Preoperative prophylactic antibiotics rapidly cross the placenta exposing babies to high dose broad spectrum antibiotics around the time of birth.^9^ Although no short-term harms to the baby have been reported,^6^ intrapartum antibiotics have been shown to alter the gut microbiota of newborns.^10^ There is growing evidence that the composition of gut microbes in infants plays a role in their immune system development including response to different antigens and inflammation and is associated with susceptibility to asthma, allergies and other immune-related diseases later in life.^11–18^ There is a paucity of research regarding the longer term effect of preincision prophylactic antibiotics for CS on child health.

### Aim

The overall aim of this research study is to investigate whether the change in the guidance from recommending prophylactic antibiotics after cord clamping to preincision antibiotics has had any effect on the incidence of allergic and other related health conditions in children born by CS in the UK. This study will provide evidence on long-term impacts of CS preoperative prophylactic antibiotics to inform current guidance regarding the timing of administration of these antibiotics. It will either reinforce the current recommendation or, if negative impacts on child health are observed, will enable assessment of the magnitude of the risks against the benefits of reduced maternal morbidity.

### Objectives

The primary objective of the study is to investigate whether preincisional in-utero exposure to antibiotics immediately prior to birth (Intervention) compared with no preincisional antibiotic exposure (Comparator) increases the risk of 1) asthma and 2) eczema (Outcomes) in children born by CS (Population). The relationship between antibiotic exposure and asthma and eczema severity (defined based on prescribing information and hospital admission data) will also be explored.

Secondary objectives:

Investigating the effect of preincision prophylactic antibiotics in children born by CS on: a) other allergic and allergy-related diseases; b) autoimmune diseases; c) infections and inflammation; d) other immune system-related conditions; e) neurodevelopmental conditions; f) less specific measures of child health (colic and failure to thrive).Investigating the effect of preincision prophylactic antibiotics in children born by CS on health service utilisation (overall consultation frequency in primary care and hospital admissions).Investigating if the effects of a reduction in postpartum maternal infectious morbidity shown in randomised controlled trials outside the UK can be replicated in the UK using routine healthcare data.

## Methods and analysis

### Study design

To address the primary objective and secondary objectives 1 and 2, a controlled interrupted time series study will be undertaken using a cohort of women and their children born between 2006 and 2018 in the UK who are included in two routine primary care databases, The Health Improvement Network (THIN) or Clinical Practice Research Datalink (CPRD), and the secondary care HES database.

